## ABSTRACT

**Background:** Globally, mental health (MH) challenges are increasing in prevalence, being common among youths and adolescents. This is also the case in Kenya, where available evidence has pointed to an increased prevalence of mental health disorders among young people. However, due to associated stigma and limited awareness of the MH conditions, affected individuals rarely seek mental health services. This is also partly due to the scarcity of such services and their providers. Hence, there is a need for culturally appropriate, community-based mental health services that are responsive to the needs of the youths to address the growing burden of mental health disorders among this group in Kenya.

**Objectives:** This is an implementation project that will seek to determine the effectiveness of mental health-themed music and Doing What Matters in times of stress (DWM) intervention in reducing mental health problems (psychological distress, anxiety, self-reported problems and depression) and improving the knowledge and attitude on mental health among youths in Western Kenya. Besides, the project will seek to determine the intervention's effectiveness on the resilience and functioning of the youths.

**Methods:** The project will be carried out in Bungoma and Kitale towns in Western Kenya, among youths (18-29 years) visiting selected barber shops for a routine haircut. The project will collaborate with local musicians to produce mental health-themed music to be played in selected barber shops. Selected barbers will be trained as facilitators in the delivery of doing what matters in times of stress (DWM). The barbers will use MH-themed music to initiate discussion on the project with youths visiting their barbershops. Those who consent will be screened for eligibility by research assistants, and eligible ones will be enrolled in the project by the barber. The barbers will help deliver the DWM intervention, which will last five weeks for each participant. Thereafter, selected participants will receive entrepreneurship and life skills training and support. A mixed-method approach involving a cluster randomized control trial design with each barber used as a cluster (40 clusters with 15 youths each); hence, a total of 600 youths (300 cases and 300 controls) and qualitative evaluation will be used for the evaluation. The 40 clusters will be randomised to either the intervention or control group using a randomisation ratio of 1:1. The project outcomes; depression, anxiety, stress, self-identified problems, resilience, functioning and mental health awareness will be assessed at baseline and post-intervention.

## Background

Globally, one in seven adolescents experiences a mental disorder, accounting for 13% of the global burden of disease in this age group (WHO, 2021). African Youths are disproportionately affected by mental health disorders, with a median depression and anxiety prevalence of 26.9% and 29.8%, respectively, among youths in the general population (Jörns-Presentati et al., 2021).

The scenario is no different among Kenyan youths and adolescents, with a prevalence of 28.06% and 30.38% for depressive and anxiety symptoms, respectively, among school-going adolescents (Osborn et al., 2021). A high prevalence of moderate and severe depressive symptoms of 35.7% and 5.6%, respectively, has also been reported among university students in Kenya (Othieno et al. 2014).

While limited mental health services exist due to a shortage of professional mental health service providers in the country (Kwobah et al., 2023), a previous study found that youths rarely utilise mental health services, especially those provided at health facilities. A small proportion of those who seek such services do so when it is already late, with the mean time from the onset of symptoms to the time of accessing care at the clinic being 16.6 months (Kamau et al., 2017). Besides, most of the small proportion who sought such services were referred by medical professionals or teachers (Kamau et al., 2017).

Stigmatization and discrimination of people with mental health disorders are also rife in Kenya. Approximately 81.9% of those with mental disorders in Kenya had experienced discrimination in making or keeping friends, 69.7% in finding a job, 56.3% in keeping a job, and 63.3% in dating or having an intimate relationship (Ebuenyi et al., 2019). Anticipated discrimination stopped 59.2% from applying for work, 40.8% from applying for education or training courses, and 63.4% from having a close personal relationship. Females and unemployed individuals reported significantly higher experienced discrimination than males and employed individuals. The huge treatment gap, stigma and discrimination have been highlighted to worsen the burden of mental illness (Ebuenyi et al., 2019). Besides the existing cultural barriers, the punitive penal code, which criminalizes suicide and suicidal attempts, affects the prevention, reporting, and management of mental health cases (MOH, 2020).

Previous studies in Western Kenya reported the existence of gaps in mental health in the region (Kwobah et al., 2023; Olwanda, 2021). Inadequate staff, lack of information,

funding, infrastructure, and the unavailability of psychotropic medications were noted as barriers to the utilization of mental health services (Olwanda, 2021). This necessitates low-cost, culturally appropriate and lay-delivered interventions to address the prevalent mental health needs while at the same time surmounting the barriers of limited mental health providers, limited facilities, and resources for mental health services in the region.

Recognising the magnitude of the problem, there has been an increase in efforts to develop and test psychological therapies, especially community-based ones, aimed at addressing mental health disorders (McNeish et al., 2019), with Doing What Matters in times of stress (DWM), Self Help Plus and Problem Management Plus being examples of such interventions developed by WHO (WHO, 2020). However, most of such interventions have rarely been tested among youths.

Doing What Matters in Times of Stress (DWM; WHO, 2020) is a core part of the WHO's Self Help Plus (SH+) intervention (Epping-Jordan et al., 2016), a five-session stress management course that uses pre-recorded audio complemented with an illustrated self-help book adapted for the target cultural group and can be used for large groups of up to 30 people. DWM can be delivered as lay-guided self-help and is less costly and less time-consuming. The effectiveness of the more extensive SH+ course in reducing emotional distress and improving functionality was demonstrated in a large randomized controlled trial (RCT) among South Sudanese refugees in Uganda (Tol et al., 2020). It has also been shown to prevent mental health disorders among Syrian refugees in Turkey (Acarturk et al., 2022). To the best of our knowledge, the efficacy of DWM as a standalone intervention among youth has not been tested.

To help address this gap, Sentum Scientific Solutions will utilize barbershops as a site for creating mental health awareness and providing access to youth-friendly mental health services to youths in two counties of Kenya (Bungoma and Trans-nzoia). It is projected that the intervention will help address the mental health crisis among youths in Western Kenya, which has received less attention. This project will utilise the Doing What Matters in Times of Stress (DWM) intervention to target youths experiencing mild or moderate psychological distress.

### Aims and objectives

Broadly, the project will seek to determine the feasibility and effectiveness of using local music and barber facilitated DWM to improve mental health outcomes and well-being in Western Kenya.

Specifically, the project will aim to test 1) the feasibility of using hip-hop and rap music to initiate a conversation on mental health among youths, 2) the effectiveness of the barber-delivered DWM intervention in improving mental health outcomes (depression, anxiety, stress, self-identified problems, functioning, and resilience) among participants 3) changes in knowledge, and attitude towards mental health among the youths involved in the intervention and 4) the impact of the entrepreneurship and life skills training on economic outcomes and wellbeing of the participants.

## Methods and materials

### Study design

A mixed-method study approach will be used with both quantitative and qualitative study designs. For the quantitative part, the project will utilise a two-arm, cluster randomised control trial design with an intervention and waiting list control group, with two outcomes assessment points: preintervention and post-intervention, which will be done after the five-week intervention. The qualitative design will mainly be used for process evaluation to gather in-depth information regarding the role of music in the project, understand participants' knowledge and attitude towards mental health, and assess the participants' engagement and satisfaction with the project.

### Project setting

We will implement the project in Kitale, Trans-Nzoia County and Bungoma Town, Bungoma County, within Western Kenya. We selected these sites because of limited mental health services and infrastructure (Olwanda, 2021).

We will purposely focus the project on the major towns of the two counties (Bungoma and Kitale town), where most youths are concentrated. This project will consist of four components: creating mental health awareness, identifying youth with mild and moderate psychological distress, delivering a low-cost DWM intervention with barbers as helpers/facilitators and socio-economic empowerment of selected youths with mild or moderate mental health distress who identified economic difficulties or lack of employment as their main problem.

We will implement the project in barbershops in the two study towns. Barbershops have been identified as potential areas where men securely share their views on various topics ranging from personal issues to the economy to politics, and they serve as bonding areas (Mbilishaka, 2018).

### Target population

The study will target youths aged 18 to 29 years living in urban areas of Kitale town of Trans-Nzoia county and Bungoma town in Bungoma county. The age group of 18-29 years was selected based on the scarcity of data regarding interventions targeting this age group in the targeted settings.

A total of 40 barbershops and barbers will be included in the study (20 barbershops per county). The barbershops will be invited to participate. The barbers/barbershops will act as the study clusters.

### Sample size

The target sample size for this study will be 40 barbers/barbershops (clusters) with 15 youths from each, translating to 600 youths (300 youths in the intervention group and 300 youths in the control group). The cluster-randomised trial sample calculator based on the National Institutes of Health will be used (<https://researchmethodsresources.nih.gov/>). The sample size will be determined with the ability to detect as low as Cohens d of 0.40, while taking into account an attrition rate of 20%. A statistical power of 0.8 and two-tailed alpha of 0.05 with a correlation coefficient of 0.5 between baseline and endpoint scores will be assumed. An interclass correlation of 0.02 will be assumed to allow for possible clustering effects.

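### The sample-size inputs do not lead to 600 youths: 40 clusters of 15 give about 97–99% power at d = 0.40 and a detectable effect of about 0.25–0.29 at 80% power

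*Protocol*

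**What the plan says.** All the inputs stand in one paragraph, the Sample size section of the protocol.

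- Size: "The target sample size for this study will be 40 barbers/barbershops (clusters) with 15 youths from each", that is 600 youths, 300 per arm.
- Effect: "The sample size will be determined with the ability to detect as low as Cohens d of 0.40".
- Power and alpha: "A statistical power of 0.8 and two-tailed alpha of 0.05".
- Correlation: "with a correlation coefficient of 0.5 between baseline and endpoint scores will be assumed".
- Clustering: "An interclass correlation of 0.02 will be assumed to allow for possible clustering effects".
- Attrition: "while taking into account an attrition rate of 20" per cent.

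The section names a public calculator for cluster-randomised trials but shows no output from it. The abstract and the Allocation section repeat 40 clusters of 15, randomised 1:1. The Data analysis section plans a mixed-effects linear model that adjusts for the pre-assessment score of the outcome. The protocol gives no other reason for 600: no multiplicity allowance, no higher power target, no subgroup aim and no allowance for unequal cluster sizes.

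**The concern.** The paragraph gives every input that a standard two-arm cluster calculation needs, and a size beside them. A reader takes the size to be the result of the inputs. It is not, because the inputs call for roughly half of it.

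Two explanations are possible, and they describe different trials. If the ICC of 0.02 is what the team meant, the protocol understates its power and gives a detection limit that is too high. If the team planned on a larger ICC or some other margin, an input is misstated or missing, and the trial may have little power to spare. An ethics committee or a later reader cannot tell which applies.

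**Working it through.** **Inputs** (protocol, Sample size): d = 0.40; two-sided alpha 0.05; power 0.80; ICC ρ = 0.02; baseline–endpoint correlation r = 0.5; attrition 20%; 40 clusters × 15. The 1:1 allocation in the abstract gives k = 20 clusters per arm. Attrition leaves m = 15 × 0.8 = 12 analysed per cluster. I assume equal cluster sizes and outcome SD 1, so that effects are in units of d.

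**Step 1. Try to reproduce 600 with the normal approximation.**

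n per arm = 2(1.96 + 0.842)² × f / d² × [1 + (m − 1)ρ], where f = 1 without baseline adjustment and f = 1 − r² = 0.75 with it. (A change score gives f = 2(1 − r) = 1, the same as no adjustment.)

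- Individually randomised: 99 per arm (f = 1) or 74 (f = 0.75).
- Design effect: 1 + 14 × 0.02 = 1.28 at m = 15; 1 + 11 × 0.02 = 1.22 at m = 12.
- Total after division by 0.8 for attrition: 316 (m = 15) or 300 (m = 12) with f = 1; 238 or 226 with f = 0.75.

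So the stated inputs give about 226 to 316 in total, not 600.

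**Step 2. Clusters needed, allowing for the small number of clusters.** The variance per cluster member is V, SE = √(2V / (k m)), and power comes from a noncentral t with 2(k − 1) df. The protocol gives a single r and does not say whether it also applies to cluster means, so I took both cases:

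- unadjusted: V = 1 + 11 × 0.02 = 1.22
- adjusted, r at both levels: V = 0.75 × 1.22 = 0.915
- adjusted, r at individual level only: V = 12 × 0.02 + 0.75 × 0.98 = 0.975

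Smallest k per arm with 80% power at d = 0.40 and m = 12:

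| Case | k per arm | Clusters | Youths enrolled (× 15) |
|---|---|---|---|
| Unadjusted | 12 (k = 11 gives 0.799) | 24 | 360 |
| Adjusted, both levels | 9 (0.822) | 18 | 270 |
| Adjusted, individual level only | 10 (k = 9 gives 0.798) | 20 | 300 |

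**Step 3. What 40 clusters give** (k = 20, m = 12, 38 df; critical t 2.024, 80th percentile of t 0.851). The detectable effect is (2.024 + 0.851) × SE.

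| Case | SE | d/SE at 0.40 | Power at 0.40 | Detectable d at 80% |
|---|---|---|---|---|
| Unadjusted | √(2 × 1.22/240) = 0.1008 | 3.97 | 0.972 | 0.290 |
| Adjusted, both levels | √(2 × 0.915/240) = 0.0873 | 4.58 | 0.994 | 0.251 |
| Adjusted, individual level only | √(2 × 0.975/240) = 0.0901 | 4.44 | 0.991 | 0.259 |

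**Step 4. Which ICC would make 40 × 15 give exactly 80% power at d = 0.40?** Solving Step 3 for ρ gives 0.120 unadjusted, 0.191 adjusted at both levels and 0.140 adjusted at individual level only. These are six to nine and a half times the stated 0.02.

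**Step 5. Do other readings reach 600?**

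- Whole clusters lost instead of individuals (16 per arm of 15): power 0.963 to 0.991, detectable effect 0.30 to 0.26.
- Bonferroni for four to seven outcomes: at most about 499 in total.
- Power raised to 0.95: at most about 520.

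None of these reaches 600, and the protocol states neither a Bonferroni adjustment nor a higher power.

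**The case against.** The strongest defence is that the paragraph can be read as a set of minimum requirements. It calls 600 a target, speaks of the calculator in the future tense, and never presents 600 as its output. A trial with 97–99% power does have at least 80% power, so on that reading the figures do not strictly contradict one another. This stands in part. It does not explain why 600 was chosen, and it does not rescue the wording on 0.40, which names the lowest effect that the size was set to detect. For 40 × 15 that limit is well below 0.40.

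It is also fair to say that the gap is conservative on the stated inputs. No estimate, test or type I error rate is affected. The adjusted figures do depend on whether r acts at cluster level, but this only moves the detectable effect from 0.25 to 0.26.

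A reader might infer more than the protocol supports:

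- *That the trial is underpowered.* On the stated inputs it is not. That would follow only if the true ICC were well above 0.02.
- *That real effects below 0.40 would be dismissed.* Nothing says so. The Data analysis section bases inference on two-sided P values and 95% confidence intervals, not on the planning effect.
- *That too many distressed youths are enrolled.* The protocol limits entry to non-severe distress, offers controls the intervention later, and also draws 100 participants for the entrepreneurship component. It does not give that last demand as the reason for 600, but a surplus over one calculation is not evidence of harm.
- *That 0.02 is a misprint for 0.20.* With r = 0.5 and m = 12, an ICC of 0.20 gives a total of about 589, close to 600. This is conjecture, since an ICC of 0.10 without adjustment at m = 15 gives the same total.

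**Conclusion.** The point holds as a mismatch between the stated inputs and the stated size. The inputs need about 18–24 clusters (270–360 youths), against the planned 40 clusters and 600. At 40 × 15, power for d = 0.40 is about 97% unadjusted and 99% with the planned baseline adjustment. The detectable effect at 80% power is about 0.29 and 0.25–0.26 respectively.

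These figures assume equal cluster sizes, loss of 20% within each cluster and an ICC of 0.02. The direction is reassuring only while that ICC is right. At about 0.12 (unadjusted) or 0.14–0.19 (adjusted), the same design has just 80% power. The document does not show which case applies, so the paragraph should be corrected. The number enrolled need not change.

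**What to change.** Keep 40 × 15. First check each input against the saved calculator output. Then do one of the following.

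1. If the ICC of 0.02 is confirmed, replace the power statement with, for example: *With 40 clusters, 12 youths analysed per cluster, ICC 0.02 and adjustment for baseline (r = 0.5), the trial has about 99% power for d = 0.40 and 80% power for d of about 0.25–0.26 (0.29 without adjustment).*
2. If a larger ICC or another margin was the reason for 600, state that value in place of 0.02, or state the margin, with the power it gives.

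Either way, say whether the calculation uses the 0.5 correlation through baseline adjustment and whether it is taken to apply to cluster means. The cost is one reworded paragraph.

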### Eligibility criteria

#### Youths Inclusion criteria

1. Youths aged 18-29 years seeking for services from the selected barbershops.
2. Those who consent to participate in the project.
3. Those with non-severe psychological distress (PHQ-9 Score  $\geq 5$  to  $<15$ ) and with functioning impairment (WHODAS score  $\geq 17$ ).

#### Exclusion criteria

1. Those with plans to end their lives within two weeks of the pre-assessment, hence imminent suicide attempt.
2. Those judged to have a neurological or severe mental disorder, substance use disorder or cognitive impairment.
3. Those who plan to relocate from the area within the project period.

Participants will be assessed for severe mental health disorders and neurological or substance use disorders based on a four-scale observation yes/no screening tool. A three-scale self-reporting suicide assessment scale will be administered to screen for suicidal thoughts. (Appendix III). This severe mental health neurological disorder screening tool is commonly used in community mental health intervention settings (Tol et al., 2020; Musotsi et al., 2022) and was used in the Kenyan population in a Problem Management Plus (PM+) project (Bryant et al., 2017).

The possible presence of severe mental disorders and/or cognitive impairment screening tool will not be verbally administered but reported based on observations of the research assistant undertaking screening assessments.

Those with suicide plans or severe mental health disorders will receive Psychological First Aid from the project clinical psychologist or Psychologist Research Assistants, plus referral for clinical diagnosis and management at existing public mental health facilities.

#### Barbers' eligibility criteria

We will select barbers to help the project and serve as facilitators to deliver the DWM intervention. Most are young people, with whom the visiting youths have already developed an existing rapport, hence ease of interaction.

The project team will visit the barbershops within the two study towns, discussing the project with the barbers and barbershop owners. With the barbershop owners' consent, we will recruit barbers aged 18-30 years who can read and write in English and are willing to participate in the project.

We will recruit one barber per shop so as not to interfere with normal barbershop functioning.

#### Participant recruitment

Youths will be approached by the trained barbers while visiting the barber shop for their routine haircut. The overall recruitment approach is to use music as a strategy to open dialogue on mental health between the trained barber and the youth before recruitment.

#### Intervention

Our intervention will have four components centred around the objectives. First, we will develop and use local mental health-themed music to create awareness and destigmatize mental health. The second component will involve the screening for functioning using World Health Organization Disability Assessment Schedule (WHODAS) (WHO, 2010; Ustün et al., 2010), symptoms of mental health conditions using psychometric measures Patient Health Questionnaire-9 (PHQ-9) (Kroenke et al., 2001; Kroenke et al., 2010), Psychological Outcome Profiles (PSYCHLOPS) (Ashworth et al., 2009; Ashworth et al., 2005), and Generalized Anxiety Disorder-7 (GAD-7) (Spitzer et al., 2006), Perceived Stress Scale 10 (PSS-10) (Cohen & Williamson, 1988), and resilience using Brief Resilience scale (BRS) (Smith et al., 2008). The third component will involve the use of music to initiate conversation between the barber and the youth on mental

health and the delivery of DWM interventions at the barbershop, considered a youth-friendly space, where trained and supervised barbers will facilitate the delivery of DWM to youths with mild or moderate psychological distress. The last component will involve an entrepreneurship intervention targeting selected youths with mild or moderate mental health included in the second component.

#### Music development

MHPSS experts, youths, and local musicians will collaborate to develop mental health-themed music messaging that is appropriate for the targeted youths and provides essential mental health awareness. The contracted musicians will then use the messages to compose the songs. The music will be pre-tested and validated with selected youth and refined based on feedback.

After pre-testing and validation, four local hip-hop musicians will be engaged and facilitated to produce four mental health-themed music (1 per musician) in local languages. This music will be routinely played in select barber shops in 2 counties of Kenya where the project will be conducted.

The focus of these songs will be on mental health awareness, internalized stigma and experienced discrimination. The songs will be used by the barber to create an open discussion with the youth client and awareness of mental health and mental health stigma reduction. The barbers will use these songs to initiate a conversation about the project with eligible youths visiting their shops. Those willing to participate will be recruited by the barber and referred to the study research assistant, who will carry out screening and project pre-assessment. Those found eligible will be recruited and included in the project after consenting. Those found to have severe mental health conditions will be referred to public health facilities or related projects offering services for severe mental health conditions for diagnosis and management.

